**Abstract**

**Background**

Arising pathogens are a worldwide challenge for [healthful living](https://www.thesaurus.com/browse/healthful%20living). Severe acute respiratory syndrome coronavirus 2 (COVID-19) is an enveloped RNA virus that distributed dramatically among humans. COVID-19 mainly attacks the respiratory system leading to severe acute respiratory syndrome and pneumonia. Some Rehabilitation modalities such as short waves diathermy could be of help in supporting the medical treatment and avoiding complications of COVID-19 pneumonia.

**Methods/design:** This is a single center, evaluator blinded, parallel design randomised, controlled clinical trial study protocol based on SPIRIT guidelines. A Randomization plan will be created online on [www.randomization.com](http://www.randomization.com) by a statistician who will not be part of the study. Small blocks of various sizes will be used. A total of 410 patients will be randomised in 1:1 ratio to two groups: experimental group (n=205) and control group (n=205) by permuted blocks method. The primary outcome measures will be time to positive-to-negative conversion of COVID-19 nucleic acid test in pharyngeal swab, in days assessed at 7^th^, 14^th^ ,21^st^ and 28^th^ day. The secondary outcome measures include nucleic acid test rate and recovery from symptoms, Vital signs assessment, Computed Tomography, Complete blood count, Creatine kinase, Lactate dehydrogenase, Inflammatory cytokines, Inflammatory Markers, Immune Markers and SIRS scale scores. Blinded evaluation will be at baseline (the day of starting ultra-short-wave diathermy) and after 28 days following the interventions.

**Objective:** To evaluate the therapeutic effects of ultra-short-wave diathermy (SWD) on COVID-19 pneumonia.

**Discussion**: This clinical trial will be the first randomised controlled clinical trial to comprehensively examine the efficacy of ultra-short-wave diathermy on COVID-19 pneumonia patients. The results may provide quality evidence of the role of ultra-short-wave diathermy in improving outcomes and avoiding complications of this viral infection.

**Clinical Study registration:** This randomised controlled trial had been prospectively registered with the Chinese Clinical Trials (ChiCTR2000029972) at 17, February ,2020. URL: http://www.chictr.org.cn/historyversionpuben.aspx?regno=ChiCTR2000029972

**Keywords**: COVID-19, coronavirus, Ultra short-wave diathermy, Pneumonia

**Background**

Betcoronaviruses are single strand RNA viruses hosted in variety of animals, especially mammals. The Severe acute respiratory syndrome coronavirus 2 (COVID-19), emerged as a fifth novel coronavirus in Wuhan, Hua nan sea food market [1].

This novel strain causes mild to severe pneumonia (COVID-19), initially reported in Wuhan, Central China [2-4]. The COVID-19 rapidly spread in China causing infection in 74283 people on the Mainland China, with 2009 (2.7%) deaths so far (February 19,2020) [5, 6].

As it is clear that COVID-19 can transmit from human to human [7], it was predicted that the extensive migration before Chinese New Year starting spiked the spread of virus massively to other parts of China [8]. It was suggested that COVID-19 transmitted to humans from its primary host bat through an intermediate host (non bat animals), linking to the medical histories of a cluster of infected patients suspected to be infected in Hua Nan market where wild animals are sold [9]. This strongly suggests the infection of human from the wild animals in the market and later infected people spread it to others. But the conclusion about original source, intermediate host and the originating point is still debatable because some case were found to have no relation with Hua Nan market [5, 7].

The most common initial clinical symptoms of Wuhan COVID-19 victims reported by a recent study were fever, cough, body ache or fatigue, while the less common symptoms were hemoptysis, diarrhea and headache. Some patients later developed shortness of breath, lymphopenia, while all recruited patients had pneumonia later [5]. Clinical features of 138 COVID-19 patients reported were shock, cardiac injury, acute kidney injury, acute respiratory distress syndrome and arrhythmias in many cases [6].

Till date no specific treatment exist to manage coronavirus victims [10], the present treatment is only supportive to treat the symptoms of the affected patients. The current treatment protocol includes antiviral therapy, corticosteroid therapy, respiratory support, kidney replacement therapy, Oxygen inhalation, invasive mechanical ventilation, non-invasive ventilation, extracorporeal membrane oxygenation [6].

Evidence supports the utilization of certain rehabilitation techniques like chest physiotherapy and shortwave diathermy (SWD) in the management of pneumonia and severe acute respiratory distress syndrome [11-13]. As it is known, rising temperature decline the activity and viability of viruses, SWD is among the common and essential physiotherapy modalities [13, 14]. SWD can produce an efficient deep heating in the treated area within the physiologic limits. SWD could roughly raises the muscle temperature around 15**°**C [15] in vitro / vivo studies had investigated the safety and efficacy of using SWD as a bactericidal or virucidal [16, 17]. The main principle of SWD is a non-specific action to rise the micro-organisms temperature above its thermally death point [15].

SWD also has the potential to penetrate directly into the lungs, which can promote the secretion of local anti-inflammatory factors, accelerate local blood circulation, and promote the drug to enter the infected site to exert better curative effects [13]. Moreover, SWD can significantly increase the phagocytic activity and adherence capacity of leukocytes, which increase exponentially with increasing temperature up to 40 ° C. This supports the use of short waves in early pneumonia to stimulate and enhance the body's natural defenses against microorganisms.

In 2003 SWD treatment had been hired during the SARS outbreak through combining shortwave diathermy with conventional therapy among 38 cases. The results showed that the use of short-wave as an adjuvant therapy for drug therapy has obvious effects. Utilizing short waves can speed up patient recovery and shorten hospital stays [18, 19]. Thus, according to earlier studies, using SWD could be of benefit in such viral infectious [16]. The purpose of this study is to investigate the effectiveness of Ultra shortwave diathermy in managing COVID-19(pneumonia). If shown to be effective, this intervention could be utilized for many patients, to ease up the COVID-19 associated symptoms, reduce complications and mortality, enhance recovery and decrease healthcare costs.

**Methods**

**Study design**

This is single center, evaluator blinded, parallel design randomised, controlled clinical trial study protocol, designed following the SPIRIT 2013 statement. Patient recruitment, the randomization plan, and the study events are visually described in Figure no.1.The current study was approved by the Tongji Hospital ethics committee and prospectively registered with the Chinese Clinical Trials Registry (Registry no. ChiCTR2000029972). Due to treatment nature, treatment providers and patients couldn’t be blinded in this study. However, patient evaluators and data collectors will be blinded to the intervention and group allocation. This trial will be carried out in accordance with the requirements of the "Good Clinical Practice for Drug Control (GCP)", the Helsinki Declaration and relevant laws and regulations. The intervention will be carried out in accordance with GCP, Standard Operating Procedures for clinical trials (SOP), and quality control requirements. The participants will be randomly divided into two groups: experimental group (n=205), control group (n=205). The experimental group will receive Ultra short-wave diathermy along with standard medical treatment for COVID-19 and the control group will be given only standard medical treatment for COVID-19.

**Figure no.1 Study Flow Chart**

[figure not shown]
Figure no.1 CONSORT Flow Diagram demonstrating patient flow through different events throughout the trial, Computed Tomography(CT), Complete blood count(CBC), Creatine kinase (CK) ,lactate dehydrogenase (LDH), Erythrocyte sedimentation rate ( ESR), C-reactive protein ( CRP ),  Procalcitonin ( PCT ), Cluster of Differentiation(CD), National Early Warning Score 2 (NEWS2), Systemic Inflammatory Response (SISR)

**Study population recruitment**

Patients of all genders with age range from 18 to 65 diagnosed positive for COVID-19 will be recruited from the Tongji University Hospital (Huazhong University of Science and Technology, Wuhan, China). We selected the age range 18-65 because, firstly most of the COVID-19 cases reported in Wuhan were in the given age range, and secondly patients above 65 were having a higher rate of intensive care unit (ICU) admission.

Participants will undergo preliminary screenings according to the eligibility criteria. Eligible participants will be invited to take the baseline assessment to confirm that they meet the inclusion criteria and provide written informed consent to participate. After this step, participants will be randomly divided into two groups: experimental group and a control group.

**Inclusion criteria:**

(1) Age 18-65 years.

(2) Coronavirus nucleic acid test is positive.

(3) Lung CT showed multiple patchy ground glass shadows or other typical manifestations of both lungs.

**2. Exclusion criteria:**

(1) Positive tests for other pathogens such as Tuberculosis, Mycoplasma.

(2) Patients with respiratory failure or requiring mechanical ventilation.

(3) People with metal implants or pacemaker.

(4) Those with shock.

(5) Those that have bleeding tendency or active bleeding in the lungs.

(6) Patients with multiple organ failure who need ICU monitoring and treatment.

(7) Cancer patients and those with severe underlying diseases.

(8) Pregnant or lactating women.

(9) Patients with severe cognitive impairment who cannot follow the instructions to complete the treatment.

(10) Those without signed informed consent.

(11) Those with other contraindications to short wave.

**Sample size**

The sample size for this randomised controlled trial was calculated by GPower 3.1 by using A-priori sample size calculation. Based on the values for our main variable, time to positive-to-negative conversion of COVI-19 nucleic acid test in pharyngeal swab, from another recently published study, using α=0.05, 80% power, and an effect size of 0.28, an enrolment of 390 participants would be enough to detect a statistically significant difference in time to positive-to-negative conversion of COVI-19 nucleic acid test between the two groups. Moreover 20 patients will be added to total sample to manage the expected 5% dropouts, making the total sample size 410.

**Randomization**

A Randomization plan will be created online on [www.randomization.com](http://www.randomization.com) by a statistician who will not be part of the study. A total of 410 participants will be randomised into a single treatment using randomly permuted blocks method. Small blocks of various sizes will be used so that randomization could less likely be guessed. Patients will randomly be distributed into one of the two groups in a ratio of 1:1. The randomization will be implemented with opaque envelopes.

**Blinding**This study is an evaluator blinded study. The blinding of both participants and healthcare workers is not possible in such type of intervention. Only the patient and the study physician know the randomization outcome. Other team members, patient evaluators and data collectors are blinded. After finishing the study, statistician will be present un-blinded data.

**Treatment Protocol**

**1. Groups and intervention procedures:**

After signing the informed consent, all patients will be randomly divided into the following two groups: the experimental group will be given the nationally recommended standard drug treatment + ultra-short-wave diathermy treatment; the control group will be given only the nationally recommended standard drug treatment. Each group is planned to include 205 participants.

**Short wave treatment dose:** Ultra-short-wave therapy treatment will be performed through application of ultra-short-wave therapy machine electrodes on the anterior and posterior parts of the trunk for 10 minutes, twice a day for 12 consecutive days.

**Outcome measures**

The primary outcome measures will be time to positive-to-negative conversion of COVID-19 nucleic acid in pharyngeal swab, in days. The secondary outcome measures include nucleic acid test rate and recovery from symptoms , vital signs assessment, treatment adverse effects, Vital capacity, Oxygen saturation, Computed Tomography(CT), Complete blood count(CBC), Creatine kinase (CK) ,Lactate dehydrogenase (LDH), Pharyngeal swabs RT-PCR, Inflammatory cytokines, Inflammatory Markers (Erythrocyte sedimentation rate ( ESR), C-reactive protein ( CRP ),  Procalcitonin ( PCT )), Immune Markers (CD3, CD4, CD8) and SIRS scale scores measured at baseline, after 7 days, 14 days, 21 days, and 28 days of treatment.

**Data collection tools**

Separate data collection forms are developed for trial data collection as: Medical history forms for taking relevant medical history, Case Report Form (CRF) to collect treatment related data, adverse events forms to collect data regarding any adverse event happening during the trial. For recording improvement in clinical symptoms 7-category ordinal, SIRS and NEWS2 scales will be used.

**The 7-category ordinal**

The 7-category or 7-point ordinal scale is consisting of seven separate categories. The categories range from 1-7(1,discharged from the hospital and can resume normal functions,7, death) given as: category 7 corresponds to death; category 6 patients need ICU hospitalization, require ECMO and/or invasive mechanical ventilation; category 5 patients need ICU hospitalization but do not require ECMO and/or invasive mechanical ventilation; category 4 patients are non-ICU hospitalized patients, requiring supplemental oxygen; category 3 patients are also non-ICU hospitalized patients but they do not require supplemental oxygen; category 2 patients are not hospitalized, but unable to resume normal activities; category 1, not hospitalized with resumption of normal activities [20].

| **Description** | **0 points** | **1 points** | **2 points** | **3 points** | **4 points** | **score** |
| --- | --- | --- | --- | --- | --- | --- |
| Heart beat | 60-100 | 55-59;  100-119 | 50-54;  120-140 | 41-49;  141-160 | <40;  >160 |  |
| MAP(mmHg) | 70-100 | 60-69;  101-110 | 50-59;  111-130 | 40-49;  131-159 | <40;  >160 |  |
| Respiratory rate / min | 12-20 | 9-12;  20-25 | 5-8;  26-35 | <5;  36-45 | 0;  >46 |  |
| SpO_2_（%） | >92 | 85-91 | 75-84 | 60-74 | <60 |  |
| body temperature（℃） | 36.0-37.5 | 35-35.9;  37.5-38.5 | 34-34.9;  38.6-39.5 | 33-33.9;  39.6-40 | <33;  >40 |  |
| WBC(*10^9^/L) | 4.0-10.0 | 3.0-3.9;  10.1-14.9 | 2.0-2.9;  15-20.0 | 1.0-2.0;  20.1-30.0 | <1.0;  >30.1 |  |
| GLU(mmol/L) | 3.5-5.5 | 5.7-8.6 | 8.7-13.5 | 13.6-23 | >23 |  |
| Level of consciousness | Aware/awake | Lethargy or irritability | Shallow coma | coma | brain death |  |
| **Total score :** | | | | | |  |

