**Table no.1: Systemic Inflammatory Response (SISR) Scale**

**NEWS2**

National Early Warning Score 2 (NEWS2) is commonly used for acute illness assessment based on aggregate scoring system from six physiological parameters which form the basis of scoring (respiration rate, oxygen saturation, systolic blood pressure, pulse rate, level of consciousness or new confusion, temperature). The magnitude of score allocated to every parameter shows its deviation from the normal. The score is summed and 2 points added for people requiring supplemental oxygen. The score is further categorized as: LOW score (an aggregate of 1–4), MEDIUM score (an aggregate of 5 or 6) and a HIGH score (an aggregate of 7 or more) [21].

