**Treatment period (days 7, 14, 21)**

● Evaluate and record vital signs (pulse, respiration, blood pressure, body temperature), blood oxygen saturation and vital capacity

● Laboratory tests: coronavirus nucleic acid test, Complete blood count (CBC), Creatine kinase (CK), Lactate dehydrogenase (LDH), Pharyngeal swabs RT-PCR, Inflammatory cytokines, Inflammatory Markers (Erythrocyte sedimentation rate (ESR), C-reactive protein (CRP), Procalcitonin (PCT), Immune Markers (CD3, CD4, CD8).

● Radiologic examination: Chest CT

● Other tests: ECG

● Complete symptoms evaluation: SIRS scale score, the 7-category ordinal scale, and The National Early Warning Score 2 (NEWS2)

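### The SIRS total, a named secondary outcome, is not uniquely defined: its table scores some values twice and others not at all, and no visit laboratory list names the glucose it needs

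*Protocol*

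**What the plan says.** Outcome measures names the SIRS scale score as a secondary outcome at baseline and days 7, 14, 21 and 28. The SIRS section lists eight items: heart rate, mean arterial pressure, respiratory rate, SpO2, temperature, white cell count, blood glucose and level of consciousness. Each takes 0 to 4 points, and for the seven numeric items the recorded value is looked up in Table no.1, which is printed under the heading The 7-category ordinal. Typical rows are:

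- "Heart beat | 60-100 | 55-59; 100-119 | 50-54; 120-140 | 41-49; 141-160 | <40; >160"
- "Respiratory rate / min | 12-20 | 9-12; 20-25 | 5-8; 26-35 | <5; 36-45 | 0; >46"
- SpO2: ">92 | 85-91 | 75-84 | 60-74 | <60"
- "GLU(mmol/L) | 3.5-5.5 | 5.7-8.6 | 8.7-13.5 | 13.6-23 | >23"

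Under Clinical Observation, the baseline, day 7/14/21 and day 28 visits all call for the SIRS scale. Each visit also has an itemised laboratory list, which for days 7, 14 and 21 begins "Laboratory tests: coronavirus nucleic acid test, Complete blood count (CBC), Creatine kinase (CK), Lactate dehydrogenase (LDH". It continues with the swab RT-PCR, cytokines, inflammatory markers and immune markers. Glucose is in none of the three lists.

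The NEWS2 section sums the parameter scores, adds 2 for supplemental oxygen, and then groups the result, beginning "LOW score (an aggregate of 1–4), MEDIUM score (an aggregate of 5 or 6", with 7 or more as the top group. Data collection tools lists NEWS2 for recording clinical improvement. Outcome measures does not name it.

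**The concern.** A scoring table must send every recordable value to exactly one score. This one does not, and because the protocol prints the table as its scoring rule, the fault lies in a stated rule rather than in detail left for later. Two evaluators could follow the protocol faithfully and give the same patient different totals, or find that no score applies. The SIRS section also relies on an item that the visit laboratory lists do not supply, so the eight-item total may be incomplete. What is at stake is the reproducibility of one secondary outcome at five time points.

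**Working it through.** There is no stated figure to reproduce, because the point concerns a scoring rule. The inputs are the seven numeric rows of Table no.1, the three laboratory lists under Clinical Observation, and the NEWS2 categories.

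**Step 1: coverage of each row.** Each band was coded as printed. Every value was then tested for the number of different scores it receives: exactly one is correct, two is an overlap, none is a gap. The assumed recording precision is whole numbers for heart rate, pressure, respiratory rate and SpO2, and steps of 0.1 for temperature, white cell count and glucose.

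| Item | Two scores | No score |
| --- | --- | --- |
| Heart rate | 100 (0 or 1) | 40 |
| Mean arterial pressure | none | 160 |
| Respiratory rate | 12 (0 or 1), 20 (0 or 1), 0 (3 or 4) | 46 |
| SpO2 | none | 92 |
| Temperature | 37.5 (0 or 1) | none |
| White cell count | 2.0 (2 or 3) | 30.1 |
| Glucose | none | 5.6 and all values below 3.5 |

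All seven numeric rows have at least one defect. Four rows contain overlaps (six values) and six rows contain gaps (six single values plus the low glucose range). Finer recording would add gaps: a white cell count of 3.95 falls between the band ending at 3.9 and the band starting at 4.0.

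**Step 2: effect on the total.** The maximum is 8 × 4 = 32. Each overlap lies between adjacent scores, so it moves the total by 1 point. A patient with heart rate 100, respiratory rate 20 and temperature 37.5 scores either 0 + 0 + 0 = 0 or 1 + 1 + 1 = 3 on those three items. Overlaps exist in four rows, so they can move one total by at most 4 × 1 = 4 points, and that needs four exact boundary readings at once.

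**Step 3: source of each item.** Pulse, respiration, blood pressure, temperature and SpO2 are listed at every visit, and the white cell count comes with the complete blood count. Glucose appears in 0 of the 3 laboratory lists. It carries up to 4 of the 32 points. Without it the total runs to 7 × 4 = 28.

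**Step 4: NEWS2.** Totals of 1 to 4, 5 to 6, and 7 or more each have one category. A total of 0 has none. The total is defined as a sum before any grouping, so 0 is a valid score that lacks only a label.

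**The case against.** Much of the opposing case stands and sets the size of this point.

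- **Lost signs.** Five single-value gaps (heart rate 40, pressure 160, respiratory rate 46, SpO2 92, white cell count 30.1) would close if a less-than or greater-than sign had originally included equality and lost this in text conversion. That cannot be excluded, so these five are described as printed. It does not explain the six overlaps, glucose 5.6, or the missing band below 3.5.
- **Rare values and obvious readings.** Exclusion criteria remove respiratory failure, mechanical ventilation, shock and multiple organ failure, so the extreme values should be rare. A respiratory rate of 0 has its own entry, which most scorers would let override the band below 5. The pressure row, "MAP(mmHg) | 70-100 | 60-69; 101-110 | 50-59; 111-130 | 40-49; 131-159 | <40; >160", suggests that the normal band is meant to be inclusive. These are sensible inferences, but the protocol does not state them.
- **Glucose.** A reader might infer that glucose was never measured. The documents do not show that. Each visit requires the SIRS scale, which may imply a glucose reading, and level of consciousness is also scored without being itemised as an assessment. What stands is an unreconciled difference between the SIRS section and the laboratory lists.
- **Bias.** A reader might infer a distorted treatment comparison. Evaluators and data collectors are blinded, so inconsistent scoring should mainly add noise. Nothing in the protocol shows how many patients will have boundary readings.
- **NEWS2.** A reader might infer that NEWS2 cannot be computed, or that recovered patients would drop out of its analysis. The aggregate is computable at 0, NEWS2 is not a named outcome, and no analysis of its categories is planned. Only a missing label remains.

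**Conclusion.** The point holds for SIRS. As written, the total is not uniquely defined: six values have two scores, and glucose 5.6 and all glucose below 3.5 have none. Five further single values have none if the printed signs are right. The glucose item has no named source in any visit list.

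The likely effect is inconsistent scoring of about 1 point per affected item, and a total that may lack up to 4 of its 32 points where glucose was not recorded. The conclusion assumes the recording precision given in the check and takes the printed numbers at face value. It does not depend on how often boundary values occur, which the protocol does not say. The primary outcome, time to nucleic acid conversion, is untouched. The NEWS2 omission is a separate, minor matter of labelling.

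**What to change.** Before the allocation is unblinded for analysis:

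1. Set one non-overlapping, gap-free set of bands for all seven numeric items, at the precision actually recorded and including glucose below 3.5. Name the source of the scale: the protocol cites sources for the 7-category scale and NEWS2 but none for SIRS.
2. Score every patient in both arms by program from the recorded raw values, rather than using totals assigned by evaluators.
3. Reconcile the SIRS section with the three laboratory lists on glucose. If glucose was recorded at the visits, say so and add it to the lists. If it was not, pre-specify a seven-item total (0 to 28) for both arms. An item that is never observed should not be left to the multiple imputation in the Data Analysis Plan. The Trial status section reports recruitment completed on 30/03/2020, so adding an assay at baseline is no longer possible.
4. For NEWS2, analyse the aggregate as a number or place 0 in the lowest category.

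The cost is a corrected table, a short scoring program and a check of which visits have a glucose value. No new measurement is needed.
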